## Model development and validation

Quality control will be applied throughout model development and evaluation. Model complexity will be controlled through prespecification of predictors and the use of penalised regression to reduce overfitting and ensure consistency with the available sample size. Internal validation will be performed using bootstrap resampling to assess optimism in model performance. Evidence of substantial optimism or unstable performance will be taken as an indication of overfitting and will lead to model simplification or stronger penalisation. Model performance will be judged based on both discrimination and calibration. Poor calibration or inconsistent performance across resamples will be transparently reported. Decision-curve analysis will be used as an additional check of potential clinical usefulness**.**

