## Sample size estimation

The sample size was estimated using the following formula:$$n={\left(Z\alpha /2\right)}^{2}\left(1-r^{2}\right)/d^{2}$$where Zα/2 (Confidence Interval) = 95%, CI = 1.96, r (Estimated Correlation value) = 0.6, and d (Precision) = 20%.

Considering the above values, *n* = 61

Thus, with a dropout rate of 20%. *n* = 76

Hence, the final sample size of this prospective cohort study was 76 participants with stroke.

The sample size determination is guided by a widely accepted rule of thumb for prediction modelling, which recommends approximately 10 outcome events per predictor parameter [27]. Based on this principle, the available sample size is expected to support the inclusion of a small and clinically meaningful set of predictors, anticipated to be around 7 (≈7 degrees of freedom) while minimizing the risk of overfitting. Consistent with guidance by Riley et al [28] we considered a target global shrinkage factor of ≥0.90 to limit overfitting and aimed for an anticipated discrimination performance (AUC) of approximately 0.75–0.80. Furthermore, the modelling strategy will incorporate penalised regression techniques and bootstrap-based internal validation to obtain optimism-corrected estimates of discrimination and calibration, consistent with TRIPOD recommendations.

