## Statistical methods and analysis

The data will be analysed using R Studio. The normality of the distribution will be verified via the “Kolmogorov‒Smirnov test”. If the data are normally distributed, they will be presented as the mean ± SD; if they are not normally distributed, they will be presented as the median and interquartile range. Categorical variables will be presented as frequencies and percentages, or as medians and interquartile ranges. Spearman/Pearson correlation coefficients will be applied to all predictors and outcomes. Candidate predictors will be specified by using Penalised regression methods (elastic net) for model development to achieve coefficient shrinkage and reduce overfitting.

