## Internal validation and model performance

Internal validation will be performed using bootstrap resampling to obtain optimism-corrected estimates of model performance. Model calibration will be evaluated by reporting the calibration intercept and calibration slope. Discrimination of the model will be assessed using the area under the receiver operating characteristic curve (AUC). Overall model performance will be quantified using the Brier score. The primary endpoint will be analysed as a (ΔFMA) as continuous outcome. Secondary analyses will explore clinically meaningful dichotomous thresholds for recovery based on published guidelines and expert consensus. Decision-curve analysis will be used to assess the net clinical benefit of the prediction model across a range of clinically relevant thresholds. In addition, repeated cross-validation using leave-one-out cross-validation (LOOCV) will be conducted as a sensitivity analysis to evaluate the robustness of model performance estimates.

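### A model simplified because of the bootstrap result can keep too high a corrected performance, since the plan does not place that simplification inside the resampling

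*Protocol article*

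**What the plan says.** The Protocol article describes internal validation in two places. Under Model development and validation the bootstrap is a quality check ("Internal validation will be performed using bootstrap resampling to assess optimism in model performance"), and its result feeds back into the model: "Evidence of substantial optimism or unstable performance will be taken as an indication of overfitting and will lead to model simplification or stronger penalisation". Under Internal validation and model performance the bootstrap supplies the reported figures: "Internal validation will be performed using bootstrap resampling to obtain optimism-corrected estimates of model performance".

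The text on how predictors are chosen points two ways. The quality-control text says "Model complexity will be controlled through prespecification of predictors and the use of penalised regression". The statistical methods section says "Candidate predictors will be specified by using Penalised regression methods (elastic net) for model development", which is a step that uses the outcome. The sample size section expects about 7 predictors and adds that "we considered a target global shrinkage factor of ≥0.90 to limit overfitting". That target is not tied to the revision rule.

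The article gives no value for what counts as substantial optimism, no limit on rounds of revision, no named smaller model and no penalty sequence. It does not say whether the bootstrap repeats the revision. Leave-one-out cross-validation is a sensitivity analysis, and external validation is left to future work.

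**The concern.** The rule looks at the validation result, changes the model on the same patients, and leaves the changed model as the one whose corrected performance is reported. Bootstrap correction estimates the optimism of the procedure that is rerun in each resample. If the choice of which predictors to drop was made once on the full data, and only the reduced model is then bootstrapped, the optimism from that choice is not subtracted. Rerunning the bootstrap on the reduced model does not cure this, because in each resample the reduced set is already the one that fitted the full data best.

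A rule without a numeric trigger or a named fallback cannot be coded into a resampling loop. As worded, therefore, it can only operate outside the loop.

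The internal figure is the only performance evidence this study will produce, and the article proposes that the model guide rehabilitation intensity and goal setting. An inflated figure could also favour the wrong model, by making a simplified model look better than the penalised model it replaced.

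**Working it through.** **The plan's own figure.** The sample size formula gives n = 1.96² × (1 − 0.6²) / 0.2² = 3.8416 × 0.64 / 0.04 = 61.47, stated as 61. With 20% dropout, 61 / 0.8 = 76.25, stated as 76. Both reproduce within rounding. The article gives no figure for optimism, so its size has to be simulated.

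**Inputs from the article.** 61 evaluable and 76 enrolled patients; about 7 predictors (sample size section); 9 muscles (background); r = 0.6, so R² = 0.36; a continuous primary outcome.

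**Assumptions not in the article.** Predictor correlation 0.3; ridge regression in place of elastic net; R² as the metric; a trigger of optimism in R² above 0.10; simplification as a cut to the 3 strongest predictors in the same data; a lower true R² of 0.15 or 0.20 as an alternative to 0.36.

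**Formulas.** Corrected R² = apparent R² − mean over resamples of (R² in the resample − R² of that resample's model in the full data). Excess = corrected R² − true R² of the final model in new patients.

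**Check 1: penalty tuned by leave-one-out cross-validation, n = 61, cut to 3.**

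| Candidates | Model R² | Corrected, selection outside | True | Excess | Corrected, selection repeated inside |
|---|---|---|---|---|---|
| 7 | 0.20 | 0.19 | 0.11 | 0.08 | 0.13 |
| 7 | 0.36 | 0.33 | 0.25 | 0.08 | 0.27 |
| 9 | 0.20 | 0.19 | 0.10 | 0.09 | 0.12 |
| 9 | 0.36 | 0.33 | 0.23 | 0.10 | 0.26 |

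Repeating the selection in each resample cuts the excess from 0.08–0.10 to 0.02–0.03.

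**Check 2: both branches of the rule, starting from a light fixed penalty (300 data sets, 100 resamples).** In the simplification branch, triggered data sets are cut to 3 predictors. In the penalisation branch, the penalty rises in steps until optimism is 0.10 or less. Entries are corrected / true R² (excess, from unrounded values).

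| n | Candidates | Model R² | Simplified, outside | Excess, selection inside | Penalised more, outside |
|---|---|---|---|---|---|
| 61 | 7 | 0.15 | 0.127 / 0.032 (+0.095) | +0.018 | 0.105 / 0.098 (+0.006) |
| 61 | 7 | 0.36 | 0.319 / 0.237 (+0.081) | +0.010 | 0.316 / 0.291 (+0.025) |
| 61 | 9 | 0.15 | 0.146 / 0.012 (+0.134) | +0.032 | 0.112 / 0.098 (+0.014) |
| 61 | 9 | 0.36 | 0.331 / 0.212 (+0.119) | +0.031 | 0.314 / 0.299 (+0.015) |
| 76 | 9 | 0.36 | 0.331 / 0.223 (+0.108) | +0.035 | 0.327 / 0.298 (+0.029) |
| 61 | 16 | 0.36 | 0.323 / 0.135 (+0.188) | +0.072 | 0.326 / 0.302 (+0.024) |

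The Monte Carlo standard error of each excess is 0.005 to 0.008.

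- Simplification outside the bootstrap leaves +0.08 to +0.13 with 7 to 9 candidates, and +0.19 with 16.
- Stronger penalisation outside leaves +0.01 to +0.03. The unrevised model itself has +0.01 to +0.07, so this branch adds nothing material.
- In five of the six settings the simplified model reports a higher corrected R² than the more heavily penalised one. In all six its true R² is lower.

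**Would the rule be used?** With the light penalty, optimism exceeded 0.10 in 95% to 100% of data sets. With a tuned penalty and 7 candidates it exceeded 0.10 in 86% (model R² 0.20) and 66% (0.36), and never exceeded 0.20. Use is plausible, but how often depends on a cutoff the article does not give.

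**The case against.** The strongest objection is that the article does not say predictors will be dropped by looking at outcomes. It speaks of prespecified predictors, and a cut to a clinically chosen subset fits the text equally well. Such a cut should add little bias, though it was not simulated. This stands, and it is why the point is conditional. It does not remove the point: the statistical methods section has elastic net specify the predictors, no reduced set is named, and the decision to simplify would be taken after seeing the performance results.

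Second, the article is condensed, and whether tuning and selection are repeated in each resample may be set out in a fuller plan. That the revision lies outside the bootstrap is inferred from the order and vagueness of the text. What the article does state is a rule that makes the model depend on the validation result. That rule, as fixed, can yield a wrong figure.

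Third, there are partial safeguards: penalisation, transparent reporting of poor calibration or inconsistent performance, and leave-one-out cross-validation. None is said to cover the revision step.

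A reader might go further and infer that any revision under this rule leaves performance optimistic, or that the trigger is bound to fire because full-model optimism would be 0.25 to 0.54. The documents do not support either. The penalisation branch left at most about 0.03. The 0.25 to 0.54 range comes from unpenalised least squares with 9 and 18 candidates, whereas the plan uses penalised regression with about 7. With a tuned penalty and 7 candidates, mean optimism was 0.11 to 0.13.

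**Conclusion.** The point holds for one branch of the rule and under a condition. If simplification uses the outcome data and is not repeated in each resample, the reported corrected performance of the simplified model can be too high. The excess is about 0.08 to 0.10 in R² with 61 patients, 7 to 9 candidates, a tuned penalised fit and a cut to three predictors. A light fixed penalty or more candidates makes it larger. Stronger penalisation alone is not a problem of any material size.

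The figures rest on an assumed trigger, predictor correlation, cut rule and metric, and on ridge as a stand-in for elastic net. The effect on AUC, calibration slope or Brier score was not computed. The direction does not depend on these choices, because a selection step left out of the resampling is not corrected for.

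The plan should be changed: the safeguard is cheap, and no external validation within this study would reveal the error.

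**What to change.** Revise the two validation sections together:

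- List the candidate predictors in advance, and state the elastic-net mixing value (or its grid) and how the penalty is tuned.
- State that every data-driven step (tuning, selection and any triggered simplification) is repeated inside each bootstrap resample. For a simplification rule this requires a numeric trigger and an ordered list of fallback models; if these are not wanted, drop the rule.
- Report the optimism-corrected performance of the prespecified penalised model as the primary result, whatever it is.
- Label any model simplified after seeing the bootstrap result as exploratory, and show it beside the primary model.
- Reconcile the statement that predictors are prespecified with the statement that elastic net specifies them.

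The cost is about one paragraph of wording and more computing. The reported figure will probably look less favourable. Repeating the steps is also not a perfect correction: in Check 2, repeating the selection left +0.01 to +0.04 with 7 to 9 candidates and +0.07 with 16. That is a further reason to keep the candidate list short.

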## Bias

All outcome assessments will be conducted using standardized, validated methods by trained assessors to minimize measurement error and information bias. Outcome assessors will be blinded to baseline predictor data to further minimize observer bias. To reduce attrition bias, we will employ reminders and flexible scheduling to collect follow-up data at all scheduled time points for each participant. Multiple time points will be used to gather data in order to capture longitudinal changes and increase the robustness of predictive modelling.

## Statistical methods and analysis

The data will be analysed using R Studio. The normality of the distribution will be verified via the “Kolmogorov‒Smirnov test”. If the data are normally distributed, they will be presented as the mean ± SD; if they are not normally distributed, they will be presented as the median and interquartile range. Categorical variables will be presented as frequencies and percentages, or as medians and interquartile ranges. Spearman/Pearson correlation coefficients will be applied to all predictors and outcomes. Candidate predictors will be specified by using Penalised regression methods (elastic net) for model development to achieve coefficient shrinkage and reduce overfitting.

## Internal validation and model performance

Internal validation will be performed using bootstrap resampling to obtain optimism-corrected estimates of model performance. Model calibration will be evaluated by reporting the calibration intercept and calibration slope. Discrimination of the model will be assessed using the area under the receiver operating characteristic curve (AUC). Overall model performance will be quantified using the Brier score. The primary endpoint will be analysed as a (ΔFMA) as continuous outcome. Secondary analyses will explore clinically meaningful dichotomous thresholds for recovery based on published guidelines and expert consensus. Decision-curve analysis will be used to assess the net clinical benefit of the prediction model across a range of clinically relevant thresholds. In addition, repeated cross-validation using leave-one-out cross-validation (LOOCV) will be conducted as a sensitivity analysis to evaluate the robustness of model performance estimates.

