### Dependent variables (outcome)

Primary outcome measures, including FMA (upper and lower motor assessments), ARAT, and FAC, along with secondary outcome measures such as 10MWT, Mini BEST, and SIS, will be assessed at the 1st and 3rd months post-stroke. The primary endpoint of this study will be motor recovery measured by the FMA score at 3 months post-stroke. The outcome will be analysed on a continuous scale, with clinically meaningful thresholds explored secondarily for dichotomous interpretation where appropriate. In accordance with SRRR guidelines [9], endpoint timing in this study is aligned to biologically informed recovery windows. The additional assessment at the 1st month captures the early subacute phase, which is a critical time point for neural plasticity [[30], [31], [32]]. In contrast, the 3-month time point provides a pragmatic and biologically credible primary endpoint for clinical trials of stroke recovery, consistent with SRRR recommendations.

The FMA is the recommended outcome of upper (FMA-UE) and lower extremity (FMA-LE) motor function in people with stroke. It assesses voluntary movement, coordination, and reflex activity in 33 upper extremity and 17 lower extremity items scored on a scale between 0 and 2 [33].

The ARAT assesses the activity capacity of the upper extremity. It has 19 items ordered in four subscales with hierarchical scoring: grip (4 items), grasp (6 items), pinch (6 items), and gross movement (3 items). ARAT is sensitive to changes in motor recovery and is frequently used both in clinical practice and research to evaluate functional outcomes of the paretic arm [34].

The FAC is a 6-point (scored as 0–5) functional walking assessment of ambulation ability and independence in walking, determining the level of human support needed, regardless of whether assistive devices are used [35].

The 10MWTat a comfortable walking speed is a reliable method for the assessment of walking speed in people with stroke [36]. The 10 MWT will only be assessed in participants able to walk independently (FAC≥3).

The Mini BEST includes evaluation of anticipatory and reactive postural control, sensory orientation, and dynamic gait. It comprises 14 items and has a maximum score of 28 points. Each item will be scored from 0–2, where 0 indicates the lowest and 2 denotes the highest level of function [37].

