## Uncertainty, significance and multiplicity

All key estimates will be reported, including effect sizes and 95% confidence intervals, with significant figures aligned to the measurement precision. Statistical methods will be selected based on the scale of the outcome (continuous, ordinal, or dichotomous), and model performance metrics (AUC, calibration, Brier score, and decision-curve analysis) will be reported, along with confidence intervals obtained via resampling methods. Measurement-related uncertainty arising from electrode placement, skin preparation, and normalisation procedures will be mitigated through standardised acquisition protocols, predefined quality-control thresholds, and sensitivity analyses. Multiplicity is limited by prespecifying a single primary endpoint; secondary and exploratory analyses will be interpreted cautiously, with appropriate adjustment methods applied where necessary.

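### The primary outcome is continuous, but the discrimination, overall-performance and utility measures named for the model all need a binary outcome; only calibration fits

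*Protocol article*

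**What the plan says.** **Scale of the primary endpoint.** Under *Dependent variables (outcome)*, the primary endpoint is the FMA score at 3 months: "The outcome will be analysed on a continuous scale, with clinically meaningful thresholds explored secondarily for dichotomous interpretation where appropriate". *Internal validation and model performance* keeps the scale but names a change score: "The primary endpoint will be analysed as a (ΔFMA) as continuous outcome". Whichever is meant, the outcome is continuous. Dichotomous thresholds are left to secondary exploration, and no cut-off for FMA or its change is given.

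**Performance measures.** The same section says "Discrimination of the model will be assessed using the area under the receiver operating characteristic curve (AUC") and "Overall model performance will be quantified using the Brier score". After the sentence on secondary thresholds it adds: "Decision-curve analysis will be used to assess the net clinical benefit of the prediction model across a range of clinically relevant thresholds". It also lists the calibration intercept and slope. *Uncertainty, significance and multiplicity* says that methods will follow the outcome's scale, then states that "model performance metrics (AUC, calibration, Brier score, and decision-curve analysis) will be reported".

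**Planning.** *Sample size estimation* cites an anticipated AUC of about 0.75–0.80.

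**Sensitivity check.** "repeated cross-validation using leave-one-out cross-validation (LOOCV) will be conducted as a sensitivity analysis".

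**The concern.** The study exists to develop and internally validate a prognostic model, so the performance estimates are its main result. The article is not silent about how performance will be measured. It names the measures, and most of those named cannot be calculated for the outcome it calls primary.

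An analyst following the text has two options. One is to report the primary model with calibration alone. Calibration shows whether predictions are right on average and suitably spread, but not how far a prediction typically lies from the observed score or how much variation the model explains. The other is to cut the outcome so that an AUC and Brier score can be produced. The headline result would then come from an analysis labelled secondary, at a cut-off not yet chosen, which would weaken the protection claimed from having a single primary endpoint.

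**Working it through.** **1. The plan's own figures.** The sample size uses z = 1.96, r = 0.6 and d = 0.20:

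n = 1.96² × (1 − 0.6²) / 0.2² = 3.8416 × 0.64 / 0.04 = 61.47 (plan: 61)

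61 / (1 − 0.20) = 76.25 (plan: 76)

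Both reproduce within rounding and are not at issue. They do show that the size was set from a correlation, a continuous-scale quantity. The AUC target of 0.75–0.80 in the same section presupposes an event, and the primary outcome defines none.

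**2. What each named measure requires.**

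| Measure | Definition | Needs | Defined for continuous FMA or ΔFMA? |
|---|---|---|---|
| ROC AUC | Probability that a participant with the event is ranked above one without | Two outcome classes | No |
| Brier score | Mean of (p − y)², with p a predicted probability and y = 0 or 1 | Binary outcome and probabilities | No |
| Decision curve (net benefit) | TP/N − (FP/N) × t/(1 − t), with t a probability threshold | Binary outcome and probabilities | No |
| Calibration intercept and slope | Observed = a + b × predicted | An observed and a predicted value | Yes |

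One of the four kinds of measure applies to the primary model.

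**3. Is a continuous measure named elsewhere?** No. R², RMSE, MAE and equivalents do not appear in the article.

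**4. Is there a cut-off that would define the binary measures?** No. Thresholds are to be explored on the basis of published guidelines and expert consensus, so AUC, Brier score and net benefit have no defined event even for the secondary analysis.

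**5. Repeated leave-one-out.** With N participants there is exactly one way to leave each out in turn, so a repeat reproduces the same N fits unless tuning is random. This was checked on simulated data (assumptions: N = 61, 7 predictors, ridge regression standing in for elastic net; the outcome scale is arbitrary and not FMA points):

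- Fixed penalty, 10 repeats: RMSE 0.910074 every time (SD about 10⁻¹⁶).
- Penalty re-tuned by random inner 10-fold splits, 10 repeats: RMSE 0.907 to 0.934, the variation coming only from the tuning step.

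Leave-one-out runs without difficulty. Only the repetition is empty.

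**The case against.** The strongest defence is that the binary measures were meant for the secondary dichotomised analyses. The article says that methods depend on the outcome's scale and that thresholds are secondary, and the decision-curve sentence directly follows the one on dichotomous thresholds. A separate analysis plan might complete the allocation.

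Part of this stands. The decision curve can fairly be read as secondary. Calibration is valid for the primary model, so a reader who inferred that every listed measure fails would be wrong.

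The defence does not rescue the AUC and Brier score. Both are stated before any dichotomy is mentioned in that section, both are attached to the model without restriction, and both recur in the later section immediately after the rule about outcome scale. Even on the charitable reading, no accuracy measure is named for the primary model. Nor is this detail left to another document, because the article does choose measures. A rank-concordance index could extend the AUC idea to a continuous outcome, but the text specifies the ROC curve.

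Two stronger inferences are tempting, and the documents support neither:

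- *That the primary analysis loses information through dichotomising.* The plan proposes neither a median split nor a refit of the primary model to a binary outcome. Continuous predictions can be compared with a cut outcome without refitting.
- *That the leave-one-out check cannot be run, or will give a biased AUC.* It can be run once. The article does not say that it is scored by AUC, and a marked downward bias would need little or no true signal together with very heavy shrinkage. With RMSE as the score that artefact does not arise.

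**Conclusion.** The point holds in a limited form. AUC and the Brier score, named as the model's discrimination and overall-performance measures, cannot be computed for the continuous primary outcome. Decision-curve analysis cannot either, though it may have been intended as secondary. Calibration intercept and slope remain, so the primary model has some valid performance measures but none for accuracy or explained variation. The AUC planning target shares the mismatch. The word *repeated* before leave-one-out is a minor slip in a sensitivity analysis.

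No numerical loss can be attached to this, since the defect is one of allocation and its effect depends on what the analyst would do in response. The conclusion rests on the primary endpoint staying continuous, as two sections state. It should be fixed before analysis, but it does not affect recruitment, measurement or the endpoint's scale.

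**What to change.** 1. **Primary (continuous) model:** report bootstrap optimism-corrected R² and RMSE or MAE in FMA points, with the calibration intercept and slope already planned.
2. **Secondary dichotomised outcome:** restrict AUC, Brier score and decision curves to it, and fix the cut-off with its source before outcome data are seen. Make the same restriction in *Uncertainty, significance and multiplicity*.
3. **Planning target:** tie the AUC of 0.75–0.80 to the secondary outcome, or restate the expected performance of the primary model as R².
4. **Sensitivity check:** use repeated k-fold cross-validation, or delete *repeated* and run leave-one-out once.

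The cost is a change of wording and a few lines of R code. No additional participants, visits or measurements are needed.

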## Procedure

All patients admitted with acute stroke to the study center during the recruitment period will be consecutively screened within the first week of stroke onset for eligibility. A screening log will be maintained to document the number of patients screened, included, excluded (with reasons), and those who decline participation. Information recorded in the screening log will inform the final participant numbers, as summarised in the study flow diagram (Fig. 1). Patients who fulfil the inclusion criteria will be requested to participate in the study. The measurements will be recorded the next day after the consent for participation. Raw sEMG signals will be collected from the paretic side at two time points—within 7 days and again at 30 days after stroke onset and processed via Lab Chart 8.1.30 software. The raw data (%Maximal Voluntary Contraction) will be normalized by the mean Root Mean Square (RMS) /max RMS X100, which will be used for analysis. Mean RMS will be computed for each 10-second trial during task execution and then averaged across trials. The following clinical assessments will be collected at the 1st and 3rd months after stroke onset: Fugl Meyer Assessment (FMA), Action Research Arm Test (ARAT), Functional Ambulation Category (FAC), 10-meter Walk Test (10MWT), Mini BEST, and Stroke Impact Scale (SIS)Version 3.0. During the hospitalization phase, all the measurements will be performed in a quiet room next to the stroke unit. During follow-up, a recording will be performed at the physiotherapy department. To minimise detection bias, assessors conducting clinical outcome assessments at the 1st and 3rd month follow-ups will be blinded to baseline sEMG measurements. Assessments will be performed by a licensed neurophysiotherapist with formal training in standardised stroke outcome measures. The investigator responsible for sEMG acquisition will be a neurophysiotherapist trained in sEMG recording, will not be involved in outcome assessments, and will remain blinded to all follow-up outcomes.

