### Measurement time points

Independent variables (predictors) will be measured at two points: within 7 days of the first-ever stroke onset and at 1st month post-stroke. Dependent variables (outcomes) will also be assessed at two points, at the 1st and 3rd months post-stroke. (Table 1)

**Table 1 tbl0001:** Time points of predictor and Outcome measure assessment.

Measures		Within 7th day	1st Month	3rd Month
**Independent Variable** (Predictor)	sEMG recording of Upper limb muscles	**✔**	**✔**	
	sEMG recording of lower limb muscles	**✔**	**✔**	
**Dependent Variable** (Outcomes)	FMA-UE		**✔**	**✔**
	ARAT		**✔**	**✔**
	FMA-LE		**✔**	**✔**
	FAC		**✔**	**✔**
	10mWT		**✔**	**✔**
	Mini-BEST		**✔**	**✔**
	SIS		**✔**	**✔**

**Abbreviation:** FMA-UE, Fugl Meyer Assessment-Upper Extremity; ARAT, Action Research Arm Test; FMA-LE, Fugl Meyer Assessment-Lower Extremity; FAC, Functional Ambulation Category; 10mWT, 10-meter Walk Test; SIS, Stroke Impact Scale.

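### The primary endpoint is defined as the 3-month FMA score but analysed as ΔFMA with no reference time, and the schedule has no week-1 FMA from which to compute change since baseline

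*Protocol article*

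**What the plan says.** All places are in the protocol article.

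- **Dependent variables (outcome):** "The primary endpoint of this study will be motor recovery measured by the FMA score at 3 months post-stroke". The same section adds: "The outcome will be analysed on a continuous scale, with clinically meaningful thresholds explored secondarily". It does not mention a change score.
- **Internal validation and model performance:** "The primary endpoint will be analysed as a (ΔFMA) as continuous outcome". This is the only place where ΔFMA appears, and it carries no reference time.
- **Measurement time points:** "Dependent variables (outcomes) will also be assessed at two points, at the 1st and 3rd months post-stroke". In Table 1, FMA-UE and FMA-LE are ticked at months 1 and 3 and not in the first-week column, which holds only sEMG. Procedure and the Abstract give the same times for the clinical assessments.
- **Which FMA score:** the primary measures are introduced as "Primary outcome measures, including FMA (upper and lower motor assessments), ARAT, and FAC". Table 1 lists FMA-UE and FMA-LE on separate rows. Uncertainty, significance and multiplicity then states: "Multiplicity is limited by prespecifying a single primary endpoint". No section says whether that endpoint is FMA-UE, FMA-LE or their total.

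**The concern.** A score at one time and a change between two times are different dependent variables. A model fitted to one need not perform well for the other. The article names the first as the endpoint and the second as what will be analysed.

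Change since the week-1 baseline would be the natural meaning of Δ, but the schedule collects nothing from which to form it. An analyst who follows the text literally is left with month 3 minus month 1. The aim in the Abstract and Background is to predict the 3-month outcome from sEMG in the first week. With a month-1 reference, recovery that takes place after the predictor is measured, but before month 1, is subtracted out of the outcome.

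At stake is whether the primary analysis addresses the study question, and whether the primary outcome is fixed before the data are seen. Leaving both the form (level or change) and the score (UE, LE or total) open means the choice could be made after seeing which is better predicted.

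**Working it through.** **1. The plan's own figure.** Sample size estimation uses n = z²(1 − r²)/d² with z = 1.96, r = 0.6 and d = 0.20:

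- n = 3.8416 × 0.64 / 0.04 = 61.47, stated as 61.
- With 20% dropout: 61 / 0.8 = 76.25, stated as 76.

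The figures reproduce apart from rounding down. The section does not say whether r = 0.6 refers to a 3-month score or to a change.

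**2. Which changes can be formed.**

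| Measure | Within 7 days | Month 1 | Month 3 |
|---|---|---|---|
| sEMG | yes | yes | no |
| FMA-UE, FMA-LE | no | yes | yes |

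The motor measures documented in week 1 are SAFE and the MRC knee extensor grade (Participants). Neither is an FMA score. Month 3 minus week 1 is therefore not computable, and month 3 minus month 1 is the only FMA difference available.

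**3. What month 3 minus month 1 covers.** Taking months as 30 and 90 days and the end of the first week as day 7:

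- Day 7 to day 90: 90 − 7 = 83 days.
- Covered by the change: 90 − 30 = 60 days, and 60/83 = 72%.
- Left out: 30 − 7 = 23 days, and 23/83 = 28%.

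These are shares of time, not of recovery. The documents give no recovery curve from which to compute the share of recovery left out.

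**4. What the change score cannot distinguish.** A participant with a high FMA at both months and one with a low FMA at both months each have a difference near zero. On the 3-month score they are at opposite ends.

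**5. Whether one correlation can serve both outcomes.** Let x be week-1 sEMG, r₁ and r₃ its correlations with month-1 and month-3 FMA, ρ the correlation between the two FMA scores, and s = SD(month 1)/SD(month 3). Then

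corr(x, month 3 − month 1) = (r₃ − r₁s) / √(1 + s² − 2ρs).

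Set r₃ = 0.6. The other inputs are assumptions, not in the documents: r₁ from 0.4 to 0.6, ρ of 0.8 or 0.9, s of 0.8 or 1.0.

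- Lowest: r₁ = 0.6, s = 1.0 gives (0.6 − 0.6)/√(2 − 2ρ) = 0.00 for either ρ.
- Highest: r₁ = 0.4, ρ = 0.9, s = 0.8 gives (0.6 − 0.32)/√(1 + 0.64 − 1.44) = 0.28/√0.20 = 0.63.

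Over this grid, a correlation of 0.6 with the 3-month score goes with anything from 0.00 to 0.63 for the change.

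**6. How much the unnamed FMA score matters.** Dependent variables (outcome) gives 33 upper and 17 lower items, each scored 0 to 2. The candidates therefore have maxima of 33 × 2 = 66 (UE), 17 × 2 = 34 (LE) and 66 + 34 = 100 (total). Participants admits people on arm weakness or on leg weakness, so a person may enter with only one limb meeting its criterion. The three scores can then be distributed quite differently in the cohort.

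**The case against.** **The article may simply be loosely worded.** ΔFMA appears once, in an ungrammatical sentence, and the authors never write month 3 minus month 1. They describe the month-1 visit as capturing the early subacute phase, not as the base of a change score. Background variables and Missing data refer generically to clinical characteristics and baseline motor severity, so an unlisted week-1 FMA cannot be ruled out entirely. This stands as a limit: month 3 minus month 1 is an inference from the schedule. It does not remove the contradiction, because the two endpoint statements differ on their face, and a week-1 FMA, if collected, is missing from a table that purports to list the time points.

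**The month-1 sEMG could pair with month 3 minus month 1.** The article does plan it: "Independent variables (predictors) will be measured at two points: within 7 days of the first-ever stroke onset and at 1st month post-stroke". But the Abstract and Background define the aim by first-week sEMG.

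**Stronger readings that a reader might infer.**

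- *That the change score would reverse a true association.* The documents do not support this. A negative correlation needs an assumed link between sEMG and speed of recovery on which they give no figure, and the grid above contains no negative value.
- *That four primary outcomes inflate family-wise error to 1 − 0.95⁴ = 18.5%.* This presumes four independent tests at 5%, which are not planned. The article separates its list of primary measures from the single primary endpoint, allows adjustment where needed, and builds an elastic-net prediction model. FMA-UE and ARAT also assess the same arm, so independence is implausible. What remains is that the FMA score is unnamed.
- *That FMA-UE adjusted for SAFE should be the sole primary.* Nothing in the documents favours it. The aim covers both limbs, and SAFE is used for eligibility and an exploratory correlation.

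**Conclusion.** The point holds as a contradiction in the primary dependent variable. It is not a detail that an article may leave to a fuller document: one section states a 3-month score, another a change without a reference time, and the schedule rules out change from week 1. The only change that can be formed omits 23 of 83 days (28%, with months as 30 and 90 days) after the predictor is recorded, and does not answer the stated question.

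The conclusion rests on Table 1 being complete for FMA. The 0.00 to 0.63 range is an illustration under assumed inputs. It shows only that r = 0.6 cannot be carried from one outcome to the other, and does not estimate the loss in this study. The unspecified FMA score is a lesser part of the same problem, because the multiplicity statement relies on one endpoint that is not fully identified. This should be corrected before any analysis.

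**What to change.** 1. Under Internal validation and model performance, replace ΔFMA with the continuous FMA score at 3 months, in line with Dependent variables (outcome).
2. State before any analysis whether the primary is FMA-UE, FMA-LE or the total. If both limbs are wanted as co-primaries, say so and name the adjustment, for example Holm.
3. If month 3 minus month 1 is kept, define it and label it exploratory.
4. In Sample size estimation, say to which outcome r = 0.6 refers.

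These are wording changes. They need no new visit or data and leave the arithmetic behind 61 and 76 unchanged.

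Alternatively, if change from baseline is really intended, add a week-1 FMA to Table 1 and the Procedure and define ΔFMA from it. That costs one more assessment in the first week, and it cannot be recovered for participants already past that week.
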